#### Accuracy Evaluation and Justification of the Sample Size

The discussion below is for IH data. The cases with KPSC and UWM data are similar. As we need to compute outcomes for the subsequent year, we essentially possess 13 years of IH data over the past 14 years. We will train and test models in a usual way. We will do a stratified 10-fold cross-validation [61] on the data in the first 12 years to train models and to estimate their accuracy. The data in the 13th year will be employed to gauge the performance of the best models, mirroring future use in clinical practice. We will select the best model using the standard performance metric AUC [61]. A care management program typically enrolls 1% to 3% of COPD patients [32]. Of the upper 1% of COPD patients the model projects to be at the highest risk of using the hospital, we will report the percentage of patients using the hospital in the subsequent year. For a program taking 1% of COPD patients based on the model’s prediction results, this percentage reflects the degree of correct enrollment. To find the variables vital for high accuracy, we will conduct backward elimination [74] to remove features on the condition that accuracy does not drop >0.02. We will compare the variables vital for high accuracy on IH data with those on KPSC and UWM data. Using the variables available in both the IH and KPSC/UWM datasets, we will build the best predictive model on IH data and compare the model’s accuracy on IH data with that on KPSC/UWM data.

We will test the hypothesis that using our techniques can boost model accuracy. To do this, we will use a 2-sided Z test to compare the AUCs of 2 predictive models built in a way like that in Obuchowski [101]. The first predictive model will use the best machine learning algorithm and take all features essential for high accuracy. The second model will be adapted from those in the literature. For each predictive model for hospital usage reported in the literature [19-28], we will retrain it on our dataset using the attributes appearing in both the original model and our dataset. The most accurate one of the retrained models will be the second model. Our hypothesis is as follows:

Null hypothesis: The first model reaches the same AUC as the second.Alternative hypothesis: The first model reaches a higher AUC than the second.

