#### Outcome Evaluation and Justification of the Sample Size

We will test the hypothesis that using our techniques can boost risk warning timeliness. To do this, for the patient cohort, we will use an *F* test to compare the number of days of early warnings provided by the 2 models mentioned in Aim 1’s accuracy evaluation section, assuming a Poisson model with an offset of 365 days. Our hypothesis is as follows:

Null hypothesis: The number of days of early warning provided by the first model is the same as that provided by the second.Alternative hypothesis: The number of days of early warning provided by the first model is larger than that provided by the second.

Assuming the number of days of early warning has an exponential distribution and employing an *F* test at a one-sided significance level of 0.05, a sample size of 600 patients offers 80% power to detect a minimum raise of 27.8 days of early warning by the first model, when the second model warns, on average, 180 days in advance. About 2000 COPD patients ever used IH hospitals during the 14th year, giving enough power to test our hypothesis. The conclusion remains valid if the actual situation differs somewhat from the assumed one.

For Aims 1 and 2, our goal is to reach a boost of ≥0.1 in accuracy and ≥30 days in risk warning timeliness, respectively. If we cannot reach this goal on the entire COPD patient group, we will construct distinct models for differing patient subgroups. The patient subgroups are described by characteristics such as age or co-morbidity, which are often independent variables in the original predictive models. If we still cannot reach this goal, we will do subanalyses to find the patient subgroups, for which our predictive models show good performance, and then apply our ultimate predictive models only to these patient subgroups.

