#### Justification of the Sample Size

Assuming a moderate intra-class correlation of 0.1 within the same care manager on the outcome of whether the perceived care plan quality is improved, a sample size of 40 instances per care manager for 10 care managers is equivalent to totally 82 independent instances after adjusting for the clustering effect. At a 2-sided significance level of 0.05, we will have 80% power to identify a 9.7% increase in the odds of improving the perceived care plan quality with actionable information. A similar conclusion holds if the actual correlation differs somewhat from the assumed one.

If giving actionable information has no significant impact on the perceived care plan quality on the whole group of COPD patients, we will do subanalyses to find those patient subgroups on which significant impact occurs.

### Experiment 2

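### When a goal is missed or a test is not significant, the plan selects patient subgroups by their observed results without keeping that selection apart from the data that report those results

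*Protocol article*

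**What the plan says.** The last paragraph of Aim 2, Outcome Evaluation and Justification of the Sample Size, covers Aims 1 and 2 together: "our goal is to reach a boost of ≥0.1 in accuracy and ≥30 days in risk warning timeliness, respectively". It then sets out two fallback steps.

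- If the goal is missed on the whole COPD group, "we will construct distinct models for differing patient subgroups". The subgroups are only illustrated: "The patient subgroups are described by characteristics such as age or co-morbidity".
- If it is still missed, "we will do subanalyses to find the patient subgroups, for which our predictive models show good performance". Use of the final models is afterwards restricted to the patients so selected.

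Aim 5, Experiment 1, Justification of the Sample Size, has a similar rule. If the overall effect on perceived care plan quality is not significant, "we will do subanalyses to find those patient subgroups on which significant impact occurs".

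On the data, Aim 1, Accuracy Evaluation and Justification of the Sample Size, uses the first 12 years of Intermountain Healthcare (IH) data for training and cross-validation. Of the remainder it says: "The data in the 13th year will be employed to gauge the performance of the best models". The outcome section of Aim 2 measures warning days in patients who used the hospital in year 14. The Datasets section shows that IH data end in 2018, which is year 14.

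**The concern.** Both rules start from a disappointing result and select on the observed result: performance in Aims 1 and 2, significance in Experiment 1. In Aims 1 and 2 the selection has a consequence, because it decides which patients the final models serve.

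The best-looking of several subgroups owes part of its rank to chance. If the same data both pick it and report its performance, the reported gain is too high. Aim 2 is the clearest case. Whether the 30-day goal was met is seen on the year-14 cohort, the remodelling and search follow from that, and no later IH year is set aside. Data from the two other health care systems exist, but the plan does not assign them to confirming selected subgroups.

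At stake are an overstated gain in accuracy or warning time in the selected patients, a model scope defined partly by noise, and a hold-out that no longer mirrors future use.

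**Working it through.** **Inputs from the protocol.** Goals of 0.1 and 30 days; about 2000 IH COPD patients with hospital use in year 14; mean warning of 180 days under the comparator model; exponential distribution (all Aim 2). About 35,000 COPD patients and a correlation of 0.6 between models (Aim 1). A 2-sided level of 0.05 (Experiment 1). **Assumed:** the number k of equal, disjoint subgroups, and the true gains.

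**1. The plan's own Aim 2 figure.** It states that "at a one-sided significance level of 0.05, a sample size of 600 patients offers 80% power" for a gain of 27.8 days over 180, a ratio of 207.8/180 = 1.1544. For two independent exponential samples of n each, power = P(F(2n,2n) > F(0.95; 2n,2n)/1.1544). At n = 600 per model this is 0.8001, so the figure reproduces. It treats the two models' results as independent samples, and step 2 first does the same.

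**2. Selection in Aim 2.** Let the true gain be 15 days in every subgroup, so that the goal is truly missed everywhere. With m = 2000/k patients, the observed gain has SD √(195² + 180²)/√m = 265.4/√m. A subgroup reaches 30 days with probability p = P(Z > 15/SD), and at least one does with probability 1 − (1 − p)^k.

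| k | m | SD (days) | p | at least one ≥30 days |
|---|---|---|---|---|
| 1 | 2000 | 5.9 | 0.006 | 0.6% |
| 4 | 500 | 11.9 | 0.103 | 35% |
| 8 | 250 | 16.8 | 0.186 | 81% |
| 10 | 200 | 18.8 | 0.212 | 91% |

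Simulation from the exponential model agrees (34.9%, 80.4% and 90.7% for k = 4, 8 and 10). The mean observed gain in the best subgroup is then 27, 39 and 44 days, against a true 15. With no true gain, the simulated chance is 1.6%, 22% and 38%.

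*Sensitivity to pairing.* Both models are scored on the same patients, so their warning days are probably positively correlated. Borrowing 0.6 from Aim 1 as an assumption, the SD becomes √(70,425 − 2 × 0.6 × 195 × 180)/√m = 168.2/√m. For k = 4, 8 and 10 this is 7.5, 10.6 and 11.9 days; p is 0.023, 0.079 and 0.104; and the chance is about 9%, 48% and 67%. The problem is smaller but remains.

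**3. Selection on the AUC gain.** The Obuchowski approximation at AUC 0.8, with about 16 non-users per user (33,000/2000 = 16.5) and correlation 0.6:

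- a = 1.414 × 0.8416 = 1.190, so a² = 1.416.
- V = 0.0099 × e^(−0.708) × [(5 × 1.416 + 8) + (1.416 + 8)/16] = 0.0764.
- Variance of the difference = 2 × 0.0764 × (1 − 0.6)/n = 0.0611/n, with n users per subgroup.
- k = 10, n = 200: SE 0.0175. The expected maximum of 10 standard normals is 1.54, so the bias is about 0.027.
- k = 20, n = 100: SE 0.0247. The expected maximum of 20 is 1.87, so the bias is about 0.046.

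That is 27% to 46% of the 0.1 goal, if the selection is made on the year-13 data.

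**4. Experiment 1.** With no effect, each 2-sided test at 0.05 is falsely favourable with probability 0.025. The chance of at least one such subgroup is 1 − 0.975^k: 12%, 22% and 40% for k = 5, 10 and 20 independent subgroups.

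**The case against.** **The search data are not named.** The fallback paragraph does not say where subgroups are sought, and Aim 1 uses cross-validation on the first 12 years to estimate accuracy. A reader might infer that the year-13 data will be used for tuning in both aims. For Aim 1 the text does not establish this, and a search inside the development years would be compatible with it. The objection is weaker for Aim 2, whose goal is measured on the year-14 cohort.

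**No claim is promised.** A reader might infer that the plan will claim success in the subgroups. It says only that models will be applied there, or that subgroups will be found. The whole-cohort tests are specified first and nothing withdraws them. Limiting a model to patients in whom it works can be a legitimate choice of scope. This stands, but the scope still rests on performance estimates that selection inflates.

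**The size can be overstated.** Using 1 − 0.95^k gives 23%, 40% and 64% for k = 5, 10 and 20. That counts unfavourable results in Experiment 1 as well, and it does not fit Aims 1 and 2, which select on a performance goal and not on a p-value. An AUC bias of 0.04 from 10 subgroups of 100 users would imply 1000 users, where the protocol has about 2000.

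**This is a condensed article.** Subgroup lists, cut-points and multiplicity rules may stand in a fuller document, and their absence is not the point here. What the article does state is a result-driven selection rule, and that is open to comment.

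**Conclusion.** The concern holds as a point that should be fixed. It does not invalidate the whole-cohort tests. The protocol states rules that select subgroups by observed performance or significance after an unfavourable result, and it does not confine the Aims 1 and 2 search to development data. For Aim 2, following the text as written exposes the only IH hold-out to the selection. Even if every subgroup truly gains only 15 days, a search over 4, 8 or 10 subgroups would find one that appears to meet the 30-day goal about 35%, 81% or 91% of the time under the plan's independence assumption, and about 9%, 48% or 67% with a correlation of 0.6. For Aim 1, an AUC bias of about 0.027 (10 subgroups) to 0.046 (20) follows only if selection uses the year-13 data. For Experiment 1, the chance of a favourable false-positive subgroup is about 12%, 22% and 40% for 5, 10 and 20 subgroups.

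All these figures assume k, equal sizes and independent subgroups. Overlapping subgroups, and the condition that the overall result has already failed, would lower them somewhat.

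**What to change.** - **Aims 1 and 2.** State that subgroup-specific modelling and any choice of subgroups will be done only within the first 12 years, by cross-validation, then frozen and evaluated once on the held-out data. Alternatively, confirm the frozen choice in another of the three health care systems.
- **All aims.** State that the whole-cohort result remains the test of each aim and is reported whatever the subgroups show.
- **Aim 5, Experiment 1.** Replace the search for significance with a few subgroups named in advance, reported through interaction estimates and labelled exploratory.

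The cost is a change of wording in two paragraphs and one analysis rule. No new data are needed, and the article says analysis had not yet begun. The investigators give up the fallback route to a favourable subgroup result.

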### Aim 3: Assess Using Temporal Features’ Potential Impact on Outcomes Via Simulations

To assess the value of a predictive model for future clinical deployment, we need to appraise care management outcomes if the model is adopted and decide how to generalize the predictive model to other sites gathering differing sets of variables. Our predictive models will be constructed on IH, KPSC, and UWM data. Our simulations will guide how to employ the predictive models in other health care systems. No previous study has decided the variables most crucial for COPD and asthma model generalization. We will apply our simulation method to care management of (1) COPD patients, (2) asthmatic children, and (3) asthmatic adults.

#### Outcomes of the Number of Inpatient Stays and the Number of Emergency Room Visits in the Subsequent Year and the Estimation Approach

The number of inpatient stays in the subsequent year is the primary outcome. The number of emergency room visits in the subsequent year is the secondary outcome. The following discussion focuses on IH data and inpatient stays. The cases with KPSC and UWM data and/or emergency room visits can be handled similarly. From statistics reported in the literature [102,103], we will obtain the percentage of inpatient stays, *p,* a care management program can help avoid. Given a set of variables, we will adopt the same method used in Aim 1 to train a predictive model on the data in the first 12 years. For the data in the 13th year, we will gather prediction results, then estimate the outcome. Consider a patient who will have *n_e_* inpatient stays in the subsequent year without enrolling in the program. If the patient gets enrolled, for each inpatient stay of the patient, we will simulate whether it will occur or not based on probability 1-*p*. The gross outcome estimate will be the sum of the estimated outcomes of all patients. Adopting a similar method, we will find the minimum accuracy required for the predictive model to be valuable in clinical practice.

#### Sensitivity Analysis

IH, KPSC, and UWM collect many variables. Another health care system may collect fewer. To ensure generalizability, we will evaluate various variable combinations and obtain the estimated outcomes when the revised model is adopted. These estimates will pinpoint crucial variables. If a crucial variable is not available in a given health care system, these estimates can hint alternative variables having minimal adverse impact on the outcomes.

We will employ a variable grouping approach relating variables likely to co-exist, such as those linked in a laboratory test panel, according to the judgment of our clinical experts. We will create and post a table showing many possible combinations of variables by groups, encompassing the trained parameters and the simulated outcomes of the predictive model. A health care system wanting to deploy the model can employ this table to estimate the expected outcomes in the system’s data environment, as well as to determine the variables to be gathered. The table has 3 columns, one for each of IH, KPSC, and UWM. Many variables collected by IH, KPSC, and UWM and used in this study are commonly available in many other systems. Thus, all variables used in each of many rows in the table will already exist in these systems.

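### The Aim 3 table appears to show own-site, size-dependent totals, so it does not directly give what a new health care system adopting the posted parameters should expect

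*Protocol article*

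**What the plan says.** The introduction to Aim 3 states the purpose: "Our simulations will guide how to employ the predictive models in other health care systems". The estimation section describes the simulation with IH as the worked example. For each chosen combination of inputs: "we will adopt the same method used in Aim 1 to train a predictive model on the data in the first 12 years". Then: "For the data in the 13th year, we will gather prediction results, then estimate the outcome". Each stay of an enrolled patient is kept with probability 1 − p, where p is the share of stays that care management avoids; p will come from the literature and no value is given. The results are added up: "The gross outcome estimate will be the sum of the estimated outcomes of all patients". KPSC and UWM are to be treated in a similar way.

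The Sensitivity Analysis section turns this into a public table with a row for each combination of variables, "encompassing the trained parameters and the simulated outcomes of the predictive model". On its layout: "The table has 3 columns, one for each of IH, KPSC, and UWM". On its use: "A health care system wanting to deploy the model can employ this table to estimate the expected outcomes". The table is also meant to help such a system decide which variables to collect. The Generalizability section of the Discussion again relies on the simulation to show how a model carries over to other sites.

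**The concern.** A system outside the study that takes over posted parameters will run a model trained elsewhere on its own patients. What it needs to know is how a model performs away from the site where it was trained. On the natural reading, no cell of the table shows this.

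The authors recognise that performance may not carry over. Aim 1 compares an IH-built model's accuracy on IH data with its accuracy on KPSC/UWM data, and Aim 4 tests generalizability in the same way. That check is not carried into the simulated outcomes, which are what outsiders are told to use.

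Two further features limit the table's use elsewhere. A total over all patients depends on how many patients the site has. And a variable may look crucial because it works where it was learned: the Aim 1 models include health care system features, such as the racial make-up of a physician's patient panel, which may not carry over. At stake are the benefit an adopting system expects and the variables it decides to gather.

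**Working it through.** **1. What each cell holds.**
- Aim 1's Final Predictive Models: a separate set of models is built for each of IH, KPSC and UWM. At UWM the models are built on, and applied to, patients who tend to receive most of their care there.
- Aim 3 estimation section: train on earlier years and simulate on a later year, with IH as the example and the other sites handled similarly. The split into 12 years and a 13th fits IH only; KPSC has 10 years of data and UWM has 7.
- Sensitivity Analysis: one column per site.

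Together these give own-site model, own-site patients, later year. This is an inference, because the table section does not say it outright, but the article describes no other content for the cells.

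**2. Effect of site size (figures from Datasets).** COPD patients = adults per year × COPD prevalence.
- IH: 878,448 × 0.041 = 36,016. The plan states about 35,000 for the 13th year, so its figure is reproduced to within 3%.
- KPSC: 2,890,027 × 0.041 = 118,491.
- UWM: 277,289 × 0.041 = 11,369 at most, before the restriction in step 1.

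KPSC/UWM = 118,491 / 11,369 = 10.4. IH/UWM = 36,016 / 11,369 = 3.2. With identical models, event rates and enrolled shares, the gross totals would stand at 3.2 : 10.4 : 1 (IH : KPSC : UWM).

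**3. Effect of moving a model to another site (illustration only).** The documents give neither p nor any cross-site accuracy, so the direction and possible size can only be explored under assumptions.
- From the plan: 35,000 patients; about 2,000 hospital users (Aim 2), an event rate of 2,000 / 35,000 = 5.7%; 1% enrolled, which is 350 patients.
- Assumed: one stay per hospital user; p = 0.2; risk scores normal with equal variance in users and non-users, separated by √2 × Φ⁻¹(AUC); the top 1% enrolled.
- Stays avoided = 350 × (share of enrolled patients who are hospital users) × p.

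| AUC at the system | Event rate | Users among enrolled | Stays avoided | Per 1,000 patients |
|---|---|---|---|---|
| 0.90 | 5.7% | 0.814 | 57.0 | 1.63 |
| 0.85 | 5.7% | 0.648 | 45.3 | 1.30 |
| 0.80 | 5.7% | 0.495 | 34.7 | 0.99 |
| 0.90 | 10% | 0.924 | 64.7 | 1.85 |
| 0.85 | 10% | 0.811 | 56.8 | 1.62 |
| 0.90 | 3% | 0.606 | 42.4 | 1.21 |

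From a source-site AUC of 0.90, a fall to 0.85 means 1 − 45.3/57.0, about 20% fewer stays avoided; a fall to 0.80 means 1 − 34.7/57.0, about 39% fewer. With no fall and the same event rate the gap is zero. A fall to 0.85 at a system with a 10% event rate is almost exactly offset (1.62 against 1.63), and with no fall a 10% event rate reverses the sign (1.85 against 1.63). Setting p = 0.4 doubles every count and leaves the percentages unchanged.

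**4. Sensitivity of a gross total.** Under the same assumptions the total over all IH patients is 2,000 − 57.0 = 1,943 stays at AUC 0.90 and 2,000 − 34.7 = 1,965 at AUC 0.80. The two differ by about 1%, because most stays belong to patients who are never enrolled. A total on this scale mainly reflects site size and hardly shows the quality of the model.

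**The case against.** The strongest reply is that the plan does more than the table alone suggests. The simulation year is later than the training years, so this is not in-sample optimism. Aim 1 compares the variables vital for accuracy across the three sites, three columns per row show whether a variable matters at one site or at all, and Aim 3 derives the minimum accuracy a model needs to be useful, which gives some link from transported accuracy to value. Patient counts can be derived from the Datasets section, so a reader could turn a total into a rate, and within one column size cancels when rows are compared. The Discussion foresees re-applying the techniques to the latest data; a system that retrains locally is closer to the own-site figure, and a cross-site figure could be too pessimistic for it. The exact unit of the cells may be left to a fuller plan. No Aim 3 hypothesis test depends on the table.

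All of this stands, and it limits the point. A reader might infer that the table overstates the benefit by a known amount, or that an outside system can make no use of it. The documents support neither. The direction depends on the new system's event rate, enrolled share, size and loss of accuracy, none of which is given, and the table remains a rough guide for a system that retrains.

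The reply does not supply the missing quantity. Dividing by patient numbers removes the effect of size but does not show how the simulated outcome changes when posted parameters are used at another site.

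**Conclusion.** The point holds in this limited form: the text promises an outside system an estimate of its own expected outcomes, while the design as described yields own-site totals. The roughly 10-fold difference between KPSC and UWM at equal performance follows from the plan's own figures. Likely optimism is a judgement that models tend to lose accuracy away from their training site. The 20% to 39% shortfall belongs to assumed AUC falls of 0.05 and 0.10 and is not an estimate for this study; it would be zero with no fall. The conclusion rests on reading each column as an own-site model, and it applies to a system that adopts the posted parameters unchanged. It is worth correcting before the table is built, but it does not affect the Aim 3 tests.

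**What to change.** For rows whose variables and cohorts are shared between sites, also apply the model trained at one site, unchanged, to the test year of the others. For adult COPD and adult asthma this gives 3 × 2 = 6 train–test pairs. For pediatric asthma it gives 2 pairs, IH and KPSC only, because UWM has adult data only. Rows with variables not shared across sites keep the own-site value alone and should be marked so.

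Label the cross-site value as the estimate for a system adopting the parameters unchanged, and the own-site value beside it as a guide for a system that retrains locally. Report stays avoided per 1,000 patients at a stated enrolled share, with the event rate and p used, and note that the UWM column rests on a selected group. Check whether variables called crucial remain so in the cross-site values. If the extra runs are not done, the Sensitivity Analysis section should narrow its claim to own-site results.

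The cost is extra computing on data that will already be in the common OMOP format, some rewording, and possibly less favourable published figures.
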